### Type of analysis

The primary analysis will be based on a difference in the number of men classified as hazardous drinkers at the 3 month assessment between the randomised groups using the intention to treat principle. This may dilute the treatment effect but the analysis will not be biased if the loss to follow up, especially for the primary outcome is similar between the two randomised groups.

Differential effects by subgroup analyses based on important prognostic factors such as age group and severity of alcohol dependence will be assessed using interaction tests. We are aware that in this exploratory trial the results of such analyses will only be indicative.

In addition, the availability of the baseline information on all participants in the Izhevsk family study II will enable us to assess the extent to which those people included in the trial differ systematically from the population sample from which they were drawn, and will provide external validation for any trial findings.

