a) Intervention group: Consent will be sought at the time of the health check by medical personnel involved. They will be trained to explain the purpose of the trial, provide written information and answer "frequently asked questions" about the trial. The consent being requested is (i) to take part in the intervention and (ii) to provide follow up data in 3 and 12 months time for the longitudinal study (even if they are not willing to take part in the intervention);

b) Control group: Consent to take part in the trial will not be sought from men randomised into the control group as they need to remain unaware of the trial (see Ethics, below). However, they will have previously given general consent to be followed up at the time of the initial re-interview.

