### Sample size

Based on current MI literature it is expected that 25% of participants in the intervention arm will stop hazardous drinking, as those in the control arm will have had minimal contact with the study and will not have been specifically told they are involved in research relating to alcohol, spontaneous reduction in hazardous drinking of more than 5% is unlikely. We have selected a difference at approximately the upper limit of the projected effect size based on previous meta-analyses [8] as a result of this unusual characteristic of the study design. We are unaware that such a Zelen design (see later) has previously been used in any study of brief alcohol intervention. Power calculations are therefore based on detecting a 20% difference between randomised groups (from 95% to 75%) with 90% power at the 5% level of statistical significance. A sample of at least 130 men (65 in each arm) will therefore be required. As randomisation was carried out prior to consent to MI, we assume that 20% of the participants in the intervention arm will not agree to receive the intervention. We also assume that there will be a 20% loss to follow for the 3 month assessment in both trial arms. This requires inflating the sample size to between 200 and 250 participants.

It should be noted that one aim of this exploratory trial will be to assess the assumptions behind these calculations in order to design a definitive study with power to assess smaller differences which could have nonetheless have major public health benefits.

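### Similar loss to follow-up in the two arms does not, as the protocol says, make the intention-to-treat comparison unbiased: loss related to drinking within an arm can still bias it, in either direction

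*Protocol article*

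**What the plan says.** Under Type of analysis, the primary comparison rests on the "difference in the number of men classified as hazardous drinkers at the 3 month assessment between the randomised groups using the intention to treat principle". The text accepts that this may dilute the treatment effect, but adds that "the analysis will not be biased if the loss to follow up, especially for the primary outcome is similar between the two randomised groups". It attaches no condition about why men are lost, or whether loss is related to drinking.

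The Sample size section treats loss as a rate: "there will be a 20% loss to follow for the 3 month assessment in both trial arms". It also says that "we assume that 20% of the participants in the intervention arm will not agree to receive the intervention".

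Under Randomisation and consent, allocation precedes the health check. Intervention men are then told of the trial and asked both to accept the intervention and to provide follow-up data, the latter even if they decline the intervention. Controls are not asked, because "they need to remain unaware of the trial"; they have given only general agreement to be recontacted. Table 1 makes the primary outcome a self-report at 3 months.

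**The concern.** Two arms can lose the same proportion of men and still be left with different mixtures of drinkers. What matters is whether, within each arm, the men lost differ in drinking from the men seen.

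This design gives the arms different situations. Intervention men know that the study concerns alcohol and have been offered counselling about it; controls know neither. A man who declined motivational interviewing or went on drinking could have a reason to avoid the 3-month interview that no control has. Equally, a man who stopped drinking could see less need to return. The Ethics section itself rests the design on the premise that knowing one is in alcohol research can change drinking.

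At stake is the reading of the primary result. Someone who relies on the sentence would see 20% against 20% lost and take the estimate as unbiased. The trial is also meant to test the assumptions for a definitive study, so a distorted effect would carry forward.

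**Working it through.** **Inputs from the Sample size section.** Hazardous drinking 95% in controls and 75% in the intervention arm; 90% power; 5% level; 65 men per arm; 20% of the intervention arm declining; 20% loss in each arm.

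**Plan's own figure.** Two-sided test, pooled variance, no continuity correction: n = [1.960·√(2 × 0.85 × 0.15) + 1.2816·√(0.95 × 0.05 + 0.75 × 0.25)]² / 0.20² = (0.990 + 0.621)² / 0.04 = 64.9, so 65 per arm. This reproduces the protocol. The inflation is also consistent: 130/(0.8 × 0.8) = 203. Alternatively, diluting the effect to 95% v 79% needs 91 per arm, and 182/0.8 = 228. Both lie in the stated 200 to 250.

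**Method for the bias.** Let p be the true hazardous rate in an arm, L = 0.20 the loss, and r the ratio of the loss rate in hazardous men to that in other men.
- Loss in non-hazardous men: L₀ = L/(p·r + 1 − p). Loss in hazardous men: L₁ = r·L₀.
- Rate among men seen: p(1 − L₁)/(1 − L).

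Total loss stays at exactly 20% in each arm; only r changes. The documents give no value of r, so every r below is an assumption.

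**A. True rates 95% v 75% (20 points), random loss in controls.**

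| r in intervention arm | L₁ | L₀ | Rate seen | Difference | Bias |
|---|---|---|---|---|---|
| 1 | 20.0% | 20.0% | 75.0% | 20.0 | 0 |
| 2 | 22.9% | 11.4% | 72.3% | 22.7 | +2.7 |
| 3 | 24.0% | 8.0% | 71.25% | 23.75 | +3.75 |
| 0.5 | 16.0% | 32.0% | 78.75% | 16.25 | −3.75 |

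For r = 2: L₀ = 0.20/(0.75 × 2 + 0.25) = 0.1143, L₁ = 0.2286, and 0.75 × 0.7714/0.8 = 0.723.

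If r = 2 in both arms, controls read 94.4% and the intervention arm 72.3%, a difference of 22.1. So the same outcome-related pattern in both arms still shifts the risk difference when there is a true effect.

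**B. Allowing for 20% refusal.** If decliners keep the control rate, the intervention-arm rate is 0.8 × 75% + 0.2 × 95% = 79%, a difference of 16 points. The protocol does not print this figure; it follows from its assumptions. With random loss in controls:
- All lost intervention men hazardous: (0.79 − 0.20)/0.8 = 73.75%. The difference reads 21.25, a bias of +5.25.
- The lost intervention men are exactly the decliners: (0.79 − 0.2 × 0.95)/0.8 = 75.0%. The difference reads 20, a bias of +4. The dilution that the protocol accepts under intention to treat has then vanished.

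**C. No true effect, all lost intervention men hazardous, random loss in controls.**
- 95% in both arms (the protocol's control rate): (0.95 − 0.20)/0.8 = 93.75%, a false benefit of 1.25 points.
- 80% in both arms (an assumption, not in the documents): (0.80 − 0.20)/0.8 = 75%, a false benefit of 5 points.

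**The case against.** The strongest reply is that the sentence is a passing remark, not a procedure. The protocol sets no threshold for similar loss, makes no decision depend on it and names no complete-case analysis. Methods for missing data are commonly left to an analysis plan or full protocol, and neither is shown. The trial calls itself exploratory. Men who decline the intervention are still asked for follow-up data, which works directly against the scenario in which every decliner is lost. The shifts at moderate loss ratios are also small: with 91 men analysed per arm at 95% v 79%, the standard error is √[(0.95 × 0.05 + 0.79 × 0.21)/91] = 4.8 points.

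Much of this stands. A reader might infer that the plan has a formal check that would certify a complete-case result; the text contains none. A reader might count the absence of an imputation method as a fault; it is not one here. The scenarios in B and C are extremes, not forecasts.

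What does not stand is the sentence itself. It names a sufficient condition for no bias, and the condition is not sufficient. No unseen document can make it true. Similar could be read to cover the kind of loss as well as the amount, but the text does not say so, and the Sample size section speaks only of a rate. Even a similar pattern of outcome-related loss gave 22.1 rather than 20 points.

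**Conclusion.** The statement is wrong as written and should be corrected. With loss fixed at 20% in each arm and random in controls, two- to threefold or halved loss among hazardous intervention men moves a true 20-point difference by about 3 to 4 points, up or down. At the 79% rate implied by refusal, the extreme in which all lost intervention men are hazardous adds 5.25 points. With no true effect, that extreme gives a false benefit of 1.25 points at 95% hazardous in both arms, or 5 at an assumed 80%.

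Two stronger readings are tempting. One is that equal loss with different reasons necessarily biases the result. It does so only if the reasons are related to drinking. The other is that the bias would favour motivational interviewing. The documents give no loss pattern, and the calculation shows bias in both directions. That the arms are likely to differ in their reasons for loss is an inference from the consent design, well supported but not stated.

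**What to change.** Replace the sentence under Type of analysis with: the estimate is unbiased only if loss to follow-up is unrelated to the outcome given arm and the baseline variables used in the analysis.

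Then:
- Compare reasons for loss, and the baseline drinking of lost men, by arm.
- Report two pre-specified sensitivity analyses covering all randomised men: missing counted as hazardous in both arms; and missing counted as hazardous in the intervention arm only, with controls imputed.
- If multiple imputation is used, let uptake of motivational interviewing enter only as an auxiliary variable for imputing the intervention arm. It arises after randomisation and exists in one arm only, so as a covariate in the analysis model it would break the intention-to-treat comparison.
- Interpret the primary result alongside these analyses. A rule allowing a claim of benefit only if the direction survives them is not needed.

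The cost is a few extra runs, recording reasons for loss where they are not already kept, and a less favourable statement about bias.

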### Aims of the study

The study is a trial to explore the efficacy and acceptability of a brief intervention aimed at reducing the prevalence of hazardous drinking in working age men in a typical Russian city (Izhevsk). This will prepare the ground for subsequent effectiveness evaluations in a range of routine service settings with different populations of hazardous drinkers. Experience conducting this trial will provide an indication of the extent of possible benefit specifically within Russia. In addition, dissemination of information about the trial and its results is expected to contribute directly to improving understanding (locally, nationally and internationally) of the nature of this major problem in Russia and the required responses.

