### Trial inclusion criteria

The men recruited into the trial will be drawn from a longitudinal observational study that is part of the Izhevsk Family Study II. This is based on 1750 men who were the controls in a case-control study of premature mortality conducted 2003–5 [7] supplemented by a further 250 men recruited using an identical protocol over a two month period in 2006. At initial recruitment to the case-control study, the men were aged 25–54 years and resident in Izhevsk. Interviews were conducted with 1750 control proxies, and 1691 of the controls themselves. For the supplementary group of 250 men, interviews were again carried out with proxies and with the men themselves. Interviewer-administered, structured questionnaires were used to gather information on a wide range of behaviours and characteristics, including alcohol consumption, tobacco use, a range of socio-economic and demographic factors, health status, and health-related behaviours.

Over an 18 month period (2007–8) as part of the longitudinal study we will attempt to recontact all of the 2000 men previously interviewed who are still alive and living in Izhevsk. Participants, who will be aged between 27 and 59 years of age, will be asked to take part in a re-interview study involving themselves as well as a proxy informant. Those who take part in this stage will then be invited to have a physical examination (referred to as a "Health Check") a few weeks later, to be carried out by a one of 4 specially trained doctors either in their own home or at a polyclinic in the city, according to the participant's preference.

Eligibility for entry to the trial will be determined according to information gathered at the initial re-interviews with proxy informants who live in the same households as the participants. These criteria are specified in Table 1. Men who had a proxy in the last study but now live alone, or for whom no proxy interview can be obtained, will be recruited on the basis of self reports of the same measures and using the same cut-offs.

**Table 1 T1:** Eligibility and outcome definitions

Eligibility/Outcome	Criteria

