Eligibility criteria for trial entry based on re-contact interview	*PROXY *reports (or self reports for men living alone) of hazardous drinking defined as one or more occurrences of any of the following: • zapoi in the past year • surrogates in the past year • hangover and/or excessive drunkenness and/or going to sleep clothed due to being drunk twice or more per week on average over the past year • weekly average of 250 mls or more of ethanol from beverages over the past year (ie 25+ UK alcohol units/week)

Primary outcome (3 months post-randomisation)	*SELF *report of hazardous drinking in defined as one or more occurrences of any of the following: • zapoi in the past month • surrogates in the past month • hangover and/or excessive drunkenness and/or going to sleep clothed due to being drunk twice or more per week on average over the past year • 250 mls or more of ethanol from beverages in the past week from beverages (ie 25+ UK alcohol units)

Secondary outcome (12 months post-randomisation)	*SELF *report of hazardous drinking defined as one or more occurrences of: • *as above at 3 months*

Supplementary secondary outcome (12 months post-randomisation)	*PROXY *report of hazardous drinking defined as one or more occurrences of: • *as above at 3 months except proxy rather than self- report* *SELF *completed: • AUDIT questionnaire (W.H.O. developed global screening assessment of hazardous drinking [26] • Leeds Dependency questionnaire [27] • SIP (Short Index of Problems) questionnaire [28] Biomarkers of: • liver damage (GGT, ALT, AST) • recent heavy drinking (CDT) [29]

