### Trial exclusion criteria

Refusal to have a baseline health check and/or refusal to be followed up at 3 and 12 months will result in exclusion from the trial.

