### Recruitment rate

Assuming that the overall prevalence of hazardous drinking remains the same over time, we have estimated from the original Izhevsk Family study data that approximately 25% of the 2000 men initially invited to take part in the Izhevsk family study II will be eligible for inclusion in the trial. Assuming a 60% response rate from those invited to participate in the Izhevsk family study 2 we would expect to be able to identify 300 hazardous drinkers eligible for the trial.

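### Comparing trial men with the whole population sample will mainly show the entry criteria, and cannot provide external validation of trial findings

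*Protocol article*

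**What the plan says.** The last paragraph of Type of analysis in the protocol article relies on "the availability of the baseline information on all participants in the Izhevsk family study II". These data are to show the extent to which trial men "differ systematically from the population sample from which they were drawn, and will provide external validation for any trial findings". The sentence thus fixes both a comparator (the whole sample) and a conclusion (external validation).

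Other sections describe how men reach the trial:

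- **Source**: "The men recruited into the trial will be drawn from a longitudinal observational study that is part of the Izhevsk Family Study II" (Trial inclusion criteria).
- **Entry criterion** (Table 1): proxy reports, or self reports for some men, "of hazardous drinking defined as one or more occurrences of any of the following: • zapoi in the past year", followed by further drinking criteria.
- **Further selection**: "Refusal to have a baseline health check and/or refusal to be followed up at 3 and 12 months will result in exclusion from the trial" (Trial exclusion criteria).
- **Expected yield** (Recruitment rate): "approximately 25% of the 2000 men initially invited to take part in the Izhevsk family study II will be eligible for inclusion in the trial". With 60% response, 300 eligible men are expected.
- **Planned size** (Sample size): 200 to 250 participants.

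Aims of the study gives the context in which the comparison would be read: "Experience conducting this trial will provide an indication of the extent of possible benefit specifically within Russia".

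**The concern.** The trial selects on drinking and the comparator does not. A table of trial men against the whole sample will show differences in drinking, and in whatever goes with drinking, even if every eligible man takes part. The question that bears on generalisability is a different one: among hazardous drinkers, do those who enter differ from those who do not? The stated comparison contains some information on this, but mixes it with the effect of the entry criterion.

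The second problem is the conclusion. A trial finding here is a randomised difference in hazardous drinking at 3 months. Men outside the trial are neither randomised nor offered MI, and the sentence names no outcome data from them. Their baseline characteristics cannot confirm or refute an effect estimate.

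What is at stake is interpretation. A report could list differences that were certain in advance, leave open whether particular kinds of hazardous drinker stayed out, and still say that its findings had been externally validated.

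**Working it through.** **Inputs.** 2000 men, 25% eligible and 60% response (Recruitment rate); 200 to 250 participants (Sample size).

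**1. The plan's own figure.** Re-interviewed: 2000 × 0.60 = 1200. Eligible among them: 1200 × 0.25 = 300. This reproduces the stated 300. Not eligible: 1200 − 300 = 900, or 75%.

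**2. Difference fixed by design.** The hazardous-drinking criterion is met by 100% of trial men and about 25% of the sample. The standardised difference is (1 − 0.25) / √[(0 + 0.25 × 0.75) / 2] = 0.75 / 0.306 ≈ 2.4, whatever the pattern of participation.

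**3. Who is outside the trial.** Among the 1200 re-interviewed men:

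| Enrolled | Outside the trial | Eligible, not enrolled | Ineligible share of those outside |
|---|---|---|---|
| 200 | 1000 | 100 | 900/1000 = 90% |
| 250 | 950 | 50 | 900/950 = 95% |

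The like-for-like group is 5% to 10% of the men outside the trial.

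**4. Effect on other traits (assumed rates, for illustration).** Suppose that eligible men enter at random, so that there is no selective participation.

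- Trait held by 50% of hazardous drinkers and 25% of others: trial 50%; whole sample 0.25 × 50% + 0.75 × 25% = 31%. The gap of 19 points comes wholly from the entry criterion.
- Trait held by 40% and 30%: trial 40%; whole sample 0.25 × 40% + 0.75 × 30% = 32.5%. The gap is 7.5 points.
- Trait held by 30% in both: no gap. For a trait unrelated to drinking, the planned comparison does not mislead.

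**5. Non-respondents.** Applied to all 2000 men, 25% gives 500 projected hazardous drinkers, so 500 − 300 = 200 would be non-respondents. Randomisation and consent and Table 2 use baseline for the recontact interview. On that reading these 200 have no baseline data and are absent from the comparison. Their eligibility is also never determined, because Table 1 sets it at the recontact interview.

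**6. If baseline meant the 2003–6 interviews.** The sample would then be all 2000 men, about 500 hazardous and 1500 not. The split is still 25% to 75%, so steps 2 and 4 are unchanged.

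**The case against.** The strongest reply is that one summary sentence in an article is being read as a full specification. It names no variables or strata. Data on all participants include the eligible men who were not enrolled, so the better comparison is possible and not ruled out. External validation may simply be loose wording for external validity, and no estimate, decision rule or hypothesis depends on it. Aims of the study claims only an indication of benefit and leaves other settings and populations to later evaluations.

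Much of this stands, and it limits the size of the point. It does not remove it, because the text does not merely omit detail: it states a comparator and a conclusion that do not match. Even if read as external validity, a comparison dominated by ineligible men is a poor way to judge it.

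Three stronger readings are tempting, and the document does not support them.

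- *The comparison cannot detect selective participation.* Too strong. Refusal of the health check or follow-up contributes to the difference between trial and sample; it is mixed with eligibility, not absent. Traits unrelated to drinking may still be informative.
- *Between 250 and 300 eligible men (500 minus 250 or 200) are left out.* This counts the 200 projected non-respondents as eligible, which is never established. Recontact is also confined to men still alive and living in Izhevsk, so some non-respondents may have died or moved. The supported figure is 50 to 100 identified eligible men.
- *The flaw undermines the definitive study.* The assumptions that Sample size says will be assessed are those behind the power calculation. None of them uses this comparison.

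**Conclusion.** The point holds as a minor one. The stated comparison will mainly reproduce the entry criteria (100% against about 25% hazardous drinking), does not isolate selection among eligible men, and cannot validate a randomised effect. About 50 to 100 identified eligible men would be outside the trial, and about 200 further projected hazardous drinkers would be non-respondents of undetermined eligibility.

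These counts assume that the plan's 25% and 60% are right, that response is unrelated to drinking, and that 200 to 250 men are enrolled. No cap on enrolment is stated: with more enrolled, fewer than 50 eligible men remain outside, and none if all 300 enter. The conclusion that baseline data cannot validate the effect depends on none of these figures.

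The primary analysis, sample size and error rates are unaffected.

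**What to change.** In Type of analysis:

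1. Make the main comparison enrolled men against re-interviewed eligible men not enrolled, on re-interview data. A comparison with the whole sample can stay as background, labelled as reflecting the entry criteria.
2. Where feasible, among men who were hazardous drinkers at the 2003–6 interviews, compare those re-interviewed with those not, on the earlier data. Report deaths and moves separately where known. Recruitment rate already estimates eligibility from the original study data, so such a classification looks possible.
3. Replace the external validation claim with a statement that the comparison describes how far trial men represent hazardous drinkers in the Izhevsk sample.

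The comparison in item 1 should be descriptive, because the groups are small. For a trait at an assumed 50%, the 95% half-width for a difference is 1.96 × √(0.25/200 + 0.25/100) ≈ 12 percentage points with 200 enrolled and 100 not, and 1.96 × √(0.25/250 + 0.25/50) ≈ 15 points with 250 and 50.

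The cost is a few tabulations of data already held or due to be collected, and one claim withdrawn. No new data collection is needed.
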